### **6.3 Other clinical and exploratory outcome assessments**

**6.3.1 Adapted Credibility/Expectancy Questionnaire.** Expectancy will be assessed using a scale asking participants to rate their answers to 3 questions that assess how much they believe that the placebo intervention that they are receiving will help the symptoms that they most want to see improve, as originally implemented by Devilly et al.

**6.3.2 Baseline and Post-Baseline Drug Use History and Assessment:** a comprehensive assessment of substance use history and treatment, environmental and psychosocial risk factors, and recent use of more than 30 commonly used licit and illicit drugs.

**6.3.3 Behavioral Inhibition/Activation System Scales (BIS/BAS):** a 24-item assessment of behavioral inhibition (BIS) and approach (BAS), wherein participants indicate on a four point Likert-like scale the extent to which each of 24 items describes their behavioral style.

**6.3.4 Pain Catastrophizing Scale (PCS):** a 13-item assessment of how pain is subjectively experienced, wherein participants indicate on a four point Likert-like scale the extent to which each of the 13 items describe the thoughts and feelings they have when they are experiencing pain.

**6.3.5 Cleveland Clinic Constipation Scoring System^30:** This constipation scoring system has 8 questions that allow patients to subjectively report the severity of their symptoms of constipation, a side effect of methadone that is most frequently reported, and which causes much discomfort.

**6.3.6 Placebo compliance assessment:** Compliance will be assessed using a VAS asking patients to rate how faithful they were in taking the placebo pill, from 0-100 (0=not faithful at all, 100=completely faithful and took the pill daily at the specified time).

**6.3.7 Methadone Symptom Severity Checklist:** This assessment is designed to have participants rate from 1-5 (with a rating of 5 being most serious) the severity of 38 symptoms of commonly-reported side effects stemming from the use of methadone.

**6.3.8 Monetary Choice Questionnaire (MCQ):** A 27-item assessment of delay discounting. For each item, the participant chooses between a smaller, immediate monetary reward and a larger, delayed monetary reward. The protocol is scored by calculating where the respondent's answers place him/her amid reference discounting curves, where placement amid steeper curves indicates higher levels of impulsivity.

**6.3.9 Barratt Impulsivity Scale, version 11 (BIS-11):** A 30-item assessment that yields information regarding three facets of trait impulsivity (i.e., attentional impulsivity, motor impulsivity and non-planning impulsivity). Participants indicate on a four-point Likert-like scale the extent to which each of 30 items describes their overall behavior. A scoring algorithm (with some items reverse-scored) yields 6 first-order and 3 second-order factors, as well as an overall score (a total possible score of 120). Higher values on each of the factors indicate higher levels of impulsivity.

**6.3.10 Exit Survey:** A 7-item quantitative and qualitative assessment of how the placebo pill was experienced by participants and their thoughts about their experience participating in the study.

## **7.0 DATA ANALYSIS**

**7.1 Sample size calculation.** We anticipate that dose escalations will be recommended at dose evaluation (approximately three weeks following entry into treatment) for approximately 70% of participants in the TAU control group. With 60 participants per group, we will have power of .80 to detect a difference between groups if the corresponding rate in the intervention group is 44% or lower (i.e., a maximum of 26/60 participants), using a Fisher exact test with a two-tailed alpha of .05. This is a medium-to-large effect, equivalent to an odds ratio of 3.03 or a Cohen's d of .61.

**7.2 Data analysis plan for pre-specified primary outcome of methadone dose.** Descriptive statistics with central tendencies and spread will be used for continuous variables; distributions and percentages will be used for categorical variables. Group differences in mean dose of methadone (in milligrams) at 90 days (primary outcome) will be tested with unpaired t-tests.

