## **6.0 OUTCOME ASSESSMENTS**

**6.1 Primary outcome.** Mean dose of methadone at 3 months (90 days) post-baseline (entry into treatment) will be recorded. These data are obtained from patient charts documenting daily records of methadone dose dispensed.

**6.2 Secondary outcome measures.** Secondary outcome measures include assessments of treatment retention, self-reported drug use, opioid withdrawal, craving, quality of life, and sleep. All measures will be obtained via facilitated self-report at all five time points, except for sleep, which will be measured only at baseline and one- and three-months post-baseline to maintain fidelity to the instrument's measure of "past-month" sleep.

**6.2.1 Treatment Retention.** Clinic attendance data will be obtained from participant Methasoft records. Three-month retention will be measured as a binomial variable (retained in treatment at the 90th day, yes/no). For descriptive purposes, retention also will be counted as the total number of days retained in treatment, starting at the participant's intake date, up to 3 months (90 days). The study team adopts the clinic's definition of discharge: 30 continuous days of treatment absence. For participants who are not retained in treatment at the 90th day, the last visit to the clinic prior to their discharge will be logged as the final day in treatment.

**6.2.2 Self-reported Drug Use.** Drug use is assessed via self-report of past-two-week use of four common substances: opiates (including heroin, fentanyl, and non-prescribed opioid use), cocaine, benzodiazepines, alcohol, and a fifth broad category of "other." The total number of days used (out of a total possible 14) will be recorded.

**6.2.3 Subjective Opiate Withdrawal Scale (SOWS).** The SOWS is a 16-item self-administered rank assessment of the severity of acute symptoms of opiate withdrawal, with anchor scores of 0 and 4 corresponding respectively to "not at all" and "extremely," for a possible total score of 64.

**6.2.4 Objective Opiate Withdrawal Scale (OOWS).** The OOWS is a 13-item experimenter-administered assessment of objective symptoms of opiate withdrawal (e.g., yawning, perspiration); symptom presence is scored a “1” for a possible total score of 13.

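### Section 7.1 states power for a week-3 escalation rate that the protocol neither lists as an outcome nor analyses; none is stated for the 90-day mean-dose t-test

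*Protocol*

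**What the plan says.** Section 7.1 begins: "We anticipate that dose escalations will be recommended at dose evaluation (approximately three weeks following entry into treatment) for approximately 70" per cent of the control group. The power claim comes next: "With 60 participants per group, we will have power of .80 to detect a difference between groups". It is conditional on at most 44% (26 of 60) being escalated on the intervention, and the test is named as well: "using a Fisher exact test with a two-tailed alpha of .05". The effect is then described as "equivalent to an odds ratio of 3.03 or a Cohen's d of .61".

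The primary outcome in Section 6.1 is a different variable: "Mean dose of methadone at 3 months (90 days) post-baseline (entry into treatment) will be recorded". Section 7.2 fixes its test: "Group differences in mean dose of methadone (in milligrams) at 90 days (primary outcome) will be tested with unpaired t-tests". Sections 2.2 and 5.1 agree that the primary comparison is of methadone dose at three months.

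A recommendation to escalate the dose is not among the outcomes in Sections 6.1, 6.2 or 6.3, and neither it nor a Fisher test appears in 7.2 or 7.3. Section 2.1 mentions limiting escalation as a broad goal, without defining it as an outcome.

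**The concern.** The variable that was powered and the variable that is tested differ in four ways:

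| | Section 7.1 | Sections 6.1 and 7.2 |
|---|---|---|
| Variable | Escalation recommended | Dose dispensed, mg |
| Scale | Binary | Continuous |
| Time | About week 3 | Day 90 |
| Test | Fisher exact | Unpaired t |

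Power for one says nothing definite about power for the other. The link would need an SD and a target difference in milligrams at day 90, and the protocol gives neither. The figure of .80 is the only power statement in the document and stands immediately before the primary analysis, so it is easily read as the power of that analysis. The planned precision of the primary comparison is in fact unstated. That matters when the result is read, and again if these pilot data support a larger application, as Section 2.3 intends.

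**Working it through.** **1. Reproduce the protocol's figure.** Inputs from Section 7.1: control rate 0.70; intervention rate 0.44, or 26/60 = 0.433; 60 per group; two-sided Fisher exact test at .05. Exact power is the sum of Bin(i; 60, 0.70) × Bin(j; 60, p) over all pairs (i, j) with Fisher p ≤ .05.

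- p = 0.44: power 0.784
- p = 26/60: power 0.806

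Both are within two points of .80, so the stated power reproduces for its own endpoint.

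**2. Trace the effect sizes.** The odds ratio is (0.70/0.30) divided by p/(1 − p).

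- p = 0.44: 2.333/0.786 = 2.97
- p = 26/60: 2.333/0.765 = 3.05

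These bracket the stated 3.03. The usual log-odds conversion, d = ln(OR) × √3/π, gives ln(3.03) × 0.5513 = 0.61. The stated d is thus the week-3 odds ratio on another scale. It is not a milligram difference divided by an SD.

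**3. What N=120 gives the primary test.** For a two-sided .05 t-test with n1 and n2 evaluable, the noncentrality is λ = d/√(1/n1 + 1/n2) on n1 + n2 − 2 degrees of freedom, and power is 1 − F(t₀.₉₇₅; df, λ), where F is the noncentral t distribution function. For example, 60/60 with d = 0.61 gives λ = 0.61/0.1826 = 3.34 on 118 df, and power 0.91.

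The protocol gives no evaluable fraction and no SD. The fractions and the SDs of 15 to 30 mg below are assumptions for illustration. The milligram difference is d × SD, for example 0.516 × 25 = 12.9.

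| Evaluable per arm | d at 80% power | mg if SD is 15 / 20 / 25 / 30 | Power if d were 0.61 |
|---|---|---|---|
| 60 (100%) | 0.52 | 7.7 / 10.3 / 12.9 / 15.5 | 0.91 |
| 42 (70%) | 0.62 | 9.3 / 12.4 / 15.5 / 18.6 | 0.79 |
| 36 (60%) | 0.67 | 10.0 / 13.4 / 16.7 / 20.1 | 0.72 |
| 30 (50%) | 0.74 | 11.0 / 14.7 / 18.4 / 22.1 | 0.64 |

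The last column is hypothetical, because nothing in the protocol links d = 0.61 to day-90 dose.

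**4. Allocation.** Section 5.5 gives both a 60:40 ratio and 30 per group per sex (60:60). That conflict is a separate matter and changes little here: at 72:48 with full data, the detectable d is about 0.53 and Fisher power at 44% is still 0.784.

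**The case against.** The strongest defence is that Section 7.1 is open about what it powers: it names the variable, the time and the test. Early escalation bears on later dose, and limiting it is a stated goal. The study presents itself as proof of concept, and a null result would be read mainly from the confidence interval for the milligram difference. All of this is fair, and it limits the damage. It still does not give the primary test a power statement.

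A reader might infer more than the document supports:

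- **That the trial is underpowered.** This is not shown. If d = 0.61 happened to hold for day-90 dose, power would be 0.91 with full data and 0.79 with 42 per arm. Adequacy depends on an SD, a target difference and an evaluable number that the protocol does not state.
- **That the calculation contains an arithmetic error.** It does not. The figures reproduce for the week-3 variable.
- **That the trial never analyses escalation.** This can be said only of the protocol. A statistical analysis plan may exist and was not available. Even if it adds such an analysis, 7.1 would still not describe the test in 7.2.
- **That heavy loss of day-90 doses is forecast.** Section 9.8 describes retention as a problem of methadone treatment in general. The dose comes from clinic dispensing records, so a missed study visit does not by itself remove it. Section 4.0 discharges patients after 30 consecutive missed days, so some may have no day-90 dose, but the number is unknown. How such cases are handled is commonly left to the statistical analysis plan.

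**Conclusion.** The stated power of .80 belongs to a week-3 binary variable that this protocol neither lists as an outcome nor analyses. For the primary test, the t-test of mean dose at 90 days, the protocol gives no power, SD or detectable milligram difference, and its d of .61 cannot fill that gap. This is an inconsistency between sizing and primary analysis within the protocol, not a detail left to a later plan.

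The size of the gap can be bounded only on the standardized scale: at 80% power the detectable d is about 0.52 with all 60 per arm, rising to about 0.62 or 0.74 if 70% or 50% are evaluable. Those fractions, and every milligram figure above, are illustrative assumptions. Whether 120 is enough is left open.

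**What to change.** In Section 7.1:

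1. Keep the Fisher calculation, because it is the only recorded basis for N=120, but say that it is that basis and not the power of the primary test. Deleting it would hide how N was chosen. The alternative is to define the week-3 escalation rate as an outcome in Section 6 with its own analysis in Section 7; relabelling alone would point to an outcome that does not exist.
2. State that the d of .61 is converted from the odds ratio of the week-3 rates.
3. Add the detectable difference of the 90-day t-test at N=120 and 80% power, in milligrams, with a justified SD and the expected number per arm with an evaluable 90-day dose. The table above can serve as a template.

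The cost is a rewording of one section, plus a source for the SD and the evaluable fraction. The stated detectable effect will look less favourable if missing doses are allowed for. Enrolment, treatment and the planned primary test do not change.

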### **7.3 Data analysis plan for secondary outcomes.**

**7.3.1 Treatment retention.** Chi-square analysis will be used to test group differences for the secondary outcome of treatment retention (continuous, up to 90 days).

**7.3.2 All other secondary outcomes.** Participants' self-reported days of drug use in the last 14 days was logged at each of the 5 total possible study visits. This information will be analyzed separately for opiates, cocaine, benzodiazepine, alcohol, and "other" drug use. For each variable, a mixed-effects longitudinal regression model will be fit to estimate and compare the mean number of days of reported drug use at each study visit by study group. The model follows:

$$\begin{aligned} \text{Expected}(\text{Numdays}_{ij}) = & \beta_0(\text{Baseline}_{ij}) + b_{0i} + \beta_{C\text{-OLP}2}(\text{C-OLP}2_{ij}) + \beta_{C\text{-OLP}3}(\text{C-OLP}3_{ij}) + \\ & \beta_{C\text{-OLP}4}(\text{C-OLP}4_{ij}) + \beta_{C\text{-OLP}5}(\text{C-OLP}5_{ij}) + \beta_{C\text{-OLP}2}(\text{TAU}2_{ij}) + \beta_{C\text{-OLP}3}(\text{TAU}3_{ij}) + \beta_{C\text{-OLP}4}(\text{TAU}4_{ij}) + \beta_{C\text{-OLP}5}(\text{TAU}5_{ij}) \end{aligned}$$

where

$\text{Numdays}_{ij}$  = Number of days of drug use for the  $i$ th person at the  $j$ th time point

$b_{0i}$  = Mean-0 normal random effect for subject  $i$ .

511 Baselineij = 1 if j=1, 0 otherwise.

512 C-OLP2ij = 1 if the patient is in the C-OLP group and time=2, 0 otherwise

513 TAU2ij = 1 if the patient is in the TAU group and time=2, 0 otherwise

514 and

515 remaining terms defined analogously.

516 By including a random effect for participant, the means are implicitly adjusted to account for  
517 differential dropout based on prior values of these variables. This model is fit using SAS proc  
518 mixed. At each time point, the hypothesis will be tested that the mean of the two groups differed.  
519 If we find that all the time-point means differed in the same direction, we would also perform a  
520 global (4 degrees of freedom) test of a difference between the groups at all four follow-up time  
521 points. For each drug analysis we will only include participants who used the drug at least once  
522 in the two weeks prior to baseline. All exploratory outcomes (OOWS, SOWS, Craving and  
523 WHO-QOL) will be analyzed in the same way as number of days of drug use, using the mixed  
524 effects longitudinal regression model.

525 **7.4 Data Collection: Retention, quality management and storage.** Participants are given an  
526 appointment card that serves as a reminder of the next date that they are to meet with study  
527 staff. Additionally, a member of the study team calls participants one day prior to the designated  
528 meeting day to remind them of their appointment. Data are collected in an in-person meeting on  
529 paper for each instrument. Following the meeting, data are recorded electronically in an ad hoc  
530 project created in RedCAP, a secure data collection and management application hosted at  
531 the University of Maryland, Baltimore. Once recorded, data are verified by a secondary  
532 independent observer and subsequently locked to prevent changes from being made. Missing  
533 data due to missed meetings are coded as incomplete. The resulting database is imported into  
534 SPSS and logical consistency checks are conducted and addressed, and missing values  
535 designated. Data collected on paper are de-identified with a Study ID number and stored in a  
536 locked cabinet in an off-site location. And electronic identifying information will be password-  
537 protected on an encrypted, HIPAA-compliant drive, and all study authors will have access to  
538 verified, cleaned and de-identified data sets.

539 **8.0 DATA AND SAFETY MONITORING PLAN**

The investigator will monitor enrollment numbers, data collection, and data concerns at regular team meetings and as needed (at least monthly) and will periodically review and ensure overall data quality and integrity. In addition, the systems used to process, and store scanned instruments and data are under two layers of password protection and on a secure off-site server. Formal statistical review of the accruing data will be conducted at the 50% mark of enrollment to check for outliers, coding errors and other problems and correct them, under [name] direction. This review will be repeated when all data are entered after enrollment is complete.

**8.1 Data collection and quality assurance plan.** Study staff will be responsible for collecting the data and entering it into the database behind a firewall. Data will be collected on paper for each instrument and is recorded electronically in an *ad hoc* project that created in REDCap, a secure data collection and management application. All source documents will be checked for completeness and accuracy at the end of each day by a secondary independent observer and subsequently locked to prevent changes from being made. Missing data due to missed meetings will be coded as incomplete. Once any data are entered into the database, any changes made to the database records are automatically recorded into an "audit trail" table. Personal health information with a code to the subject's identity will be kept on a password-protected computer behind a firewall. Only investigators for this study will have access to the data. The name with a link to the code will be kept in a locked file drawer with limited access.

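### The secondary-outcome model in section 7.3.2 rests on a random intercept alone, runs its only overall test on condition of the observed signs, and prints the wrong coefficients on the TAU terms

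*Protocol*

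**What the plan says.** Section 7.3.2 of the protocol writes out a model for days of drug use, fitted in SAS proc mixed and reused for OOWS, SOWS, craving and WHOQOL.

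- **Covariance.** The only random term is a "Mean-0 normal random effect for subject". No visit-specific variance or other residual structure is given. Baseline is part of the outcome vector, with one mean common to both arms. The section credits this term with handling dropout: "By including a random effect for participant, the means are implicitly adjusted to account for" differential dropout based on earlier values.
- **Coefficients.** The TAU indicators are defined separately (TAU2 is "1 if the patient is in the TAU group and time=2, 0 otherwise"), but the printed equation attaches C-OLP labels to them, for example "\beta_{C\text{-OLP}2}(\text{TAU}2_{ij".
- **Tests.** "At each time point, the hypothesis will be tested that the mean of the two groups differed". An overall test follows only on a condition: "If we find that all the time-point means differed in the same direction, we would also perform a" test described as "global (4 degrees of freedom) test of a difference between the groups at all four follow-up time" points. No multiplicity adjustment is stated in the section.

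Section 5.7 sets follow-up at days 14, 28, 56 and 84, so the spacing is unequal.

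**The concern.** A single random intercept implies compound symmetry: the same variance at all five visits, and the same correlation between days 0 and 84 as between days 0 and 14. There are reasons to doubt this. Baseline precedes treatment. For each drug analysis it is also restricted to people who used that drug in the previous two weeks. Because baseline sits in the outcome vector with a common mean, its modelled correlation with follow-up fixes how strongly each visit difference is adjusted for chance baseline imbalance. The same modelled covariance carries the dropout adjustment, since under likelihood-based missing-at-random reasoning it determines what earlier values say about unseen later ones.

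The testing rule is a separate matter. Whether an overall test exists depends on the observed signs, and when they disagree an outcome is judged on four separate visit tests. At least nine outcomes follow this rule (five drug categories, OOWS, SOWS, craving, WHOQOL), so at least 9 × 4 = 36 visit comparisons are made.

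Finally, an equation that gives both arms the same coefficients contains no group difference to test.

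**Working it through.** **1. The stated 4 df.** With a common baseline and separate C-OLP and TAU means at four visits, the design has 1 + 4 + 4 = 9 mean parameters. Without a group effect it has 5. So 9 − 5 = 4 df, as stated. With the coefficients exactly as printed, the design has rank 5 and the group test has 5 − 5 = 0 df. The stated 4 df is possible only with separate TAU coefficients.

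**2. Standard errors under a wrong covariance.** Inputs: n = 60 per arm (section 7.1; it cancels in the ratio), two-sided 5% (stated only in 7.1, assumed here), complete data. All variances and correlations are assumptions.

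In large samples the compound-symmetry fit settles at

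- v = mean of the five true variances
- r = (mean of the ten true covariances) / v

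The model then treats each visit difference as adjusted for baseline with slope r:

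- model variance = (2/n) · v(1 − r²)
- true variance = (2/n) · (σj² − 2r·σj0 + r²·σ0²), where 0 denotes baseline and j the visit
- type I error = 2Φ(−1.96 × SE ratio), SE ratio = model SE / true SE

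*Compound symmetry:* ratio 1.00 at every visit, error 5.0%.

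*Baseline less variable and weakly correlated* (baseline SD 2, follow-up SD 5, correlation 0.2 with baseline, 0.5 among follow-ups): v = (4 + 4×25)/5 = 20.8. Mean covariance = (4×2 + 6×12.5)/10 = 8.3, so r = 0.399. Model: 20.8 × (1 − 0.159) = 17.5. True: 25 − 2×0.399×2 + 0.159×4 = 24.0. Ratio = √(17.5/24.0) = 0.85, error 9.5%. Over baseline SD 2-3, baseline correlation 0.2-0.3 and follow-up correlation 0.5-0.6, the error is about 8-11%. Raising the follow-up correlation to 0.7 takes the top of the range to about 13%.

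*Baseline more variable* (SD 5 against 3, baseline correlation 0.3, follow-up correlation 0.5): v = (25 + 4×9)/5 = 12.2. Mean covariance = (4×4.5 + 6×4.5)/10 = 4.5, so r = 0.369. Model: 12.2 × (1 − 0.136) = 10.5. True: 9 − 2×0.369×4.5 + 0.136×25 = 9.1. Ratio 1.08, error 3.5%.

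*AR(1) 0.7 by visit, unit variances:* r = (4×0.7 + 3×0.49 + 2×0.343 + 0.240)/10 = 0.52.

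| Visit | Day 14 | Day 28 | Day 56 | Day 84 |
|---|---|---|---|---|
| SE ratio | 1.16 | 0.98 | 0.89 | 0.85 |
| Type I error | 2.3% | 5.5% | 8.0% | 9.7% |

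With assumed completely random monotone dropout to 60% completers, the AR(1) 0.7 ratios are 1.15, 0.97, 0.88 and 0.83. This checks standard errors only. The bias from dropout related to earlier values was not quantified.

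**3. The sign condition.** Under the null with compound symmetry and correlation 0.5, the baseline-adjusted visit differences have correlation 0.5/(1 + 0.5) = 1/3. The probability that all four share a sign is then about 0.30, so the overall test is skipped in about 70% of null trials. When it is run, its error is about 5%, because with a correct covariance the test statistic is independent of the sign pattern. Overall it rejects in 0.30 × 0.05 ≈ 1.5% of null trials. If the covariance is wrong, the conditional error rises, for example to 6.7-7.8% under AR(1) 0.5-0.7.

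**4. The four visit tests.** With a correct covariance, the chance under the null that at least one is significant is about 17% if the differences correlate at 0.3, and 13% at 0.7. Independence would give 1 − 0.95⁴ = 18.5%.

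**5. 4 df against 1 df.** At noncentrality (1.96 + 0.84)² = 7.85, a constant effect has 80% power on 1 df and about 60% on 4 df.

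**The case against.** The strongest reply has four parts.

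- **Direction.** A reader might infer that a random intercept understates standard errors for all these outcomes. The documents do not support that. They give no variances, correlations or dropout rates, the model is exact under compound symmetry, and it is conservative if baseline varies more than follow-up. The selection of baseline users applies to the drug analyses. Nothing says that it applies to SOWS, OOWS, craving or WHOQOL, whose baseline is taken before the first methadone dose and may be more variable. This part of the reply stands, and it is why the point is put as error in either direction.
- **The equation.** A reader might infer that no group effect would be fitted. The separate TAU indicators, the per-visit comparisons and the 4 df all show otherwise. It is a labelling error and does not itself make the tests unreliable.
- **The sign condition.** A reader might infer that selecting on sign inflates the overall test. It does not when the covariance is right. The fault is that the test is usually skipped under the null and that its existence depends on the data. A 4-df test is also defensible: the second daily pill starts in week 3, so effects may emerge late, and a 1-df average could dilute them.
- **Room for an SAP.** Covariance, degrees-of-freedom method and secondary multiplicity are often left to an SAP, and these are secondary or exploratory outcomes in a proof-of-concept trial. That limits the weight of the point. But section 7.3.2 itself writes the model, names the random effect and fixes the testing rule, so these are stated choices.

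**Conclusion.** The point holds in limited form. The random-intercept model can misstate per-visit error: 5% under compound symmetry, about 8-11% or 3.5% depending on whether baseline varies less or more than follow-up, and 2% to 10% from day 14 to day 84 under AR(1) 0.7. Every departure from 5% rests on assumed covariances, so neither size nor direction is known for this trial. The dropout adjustment depends on the same unverified structure.

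The testing rule can be judged from the text with fewer assumptions. The overall test is skipped in about 70% of null trials at correlation 0.5, and the remaining visit tests carry about a 13-17% chance of at least one false positive per outcome. The TAU labels are wrong as printed and contradict the 4-df test. The primary t-test on methadone dose is untouched. The change is worth making, but it does not threaten the trial's main conclusion.

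**What to change.** In section 7.3.2:

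1. Replace the random intercept with an unstructured covariance over the five visits (REML, Kenward-Roger degrees of freedom), keeping the common baseline mean. Reword the dropout sentence so that the adjustment rests on the likelihood and the modelled covariance under missing at random.
2. Give TAU2 to TAU5 their own coefficients.
3. Drop the sign condition and always run one pre-specified overall group test per outcome. The stated 4-df test will do. A 1-df contrast averaging the four follow-up visits is an option: it gains power for a constant effect and may lose it for a late one. Choose before the data are seen.
4. Treat visit-level differences as supportive, shown with confidence intervals.

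The cost is a few lines of SAS and protocol wording, some extra covariance parameters, and possibly slightly wider intervals.
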